### 3.1. rTMS Therapy

RTMS is delivered according to the group assignment using MagStim^®^
*Rapid*^2^ device (The Magstim Company Ltd, UK) with the D70 AirFilm figure-of-eight coil (AFC, S/N0738). Bi-phasic rTMS pulses are delivered with a pulse frequency of 5 Hz to facilitate the excitability of cHMC or iM1. Forty-two, 10-s trains of 50 pulses each are delivered at an inter-train interval of 20.3 s for a total of 2,100 pulses. Sham rTMS is delivered using another D70 AirFilm figure-of-eight sham coil (AFC Sham, S/N0101). Real rTMS elicited the activation of the targeted cortical region, while sham rTMS did not have any such physiological effect; however, the acoustic artifacts are present during real and sham stimulation. rTMS targeting is guided by MRI-stereotaxy.

Prior to starting rTMS, surface 1.8 inch diameter EMG electrodes (Adult Tape ECG Ultratrace^®^ Wet Gel, Conmed Corporation, USA) are placed over the extensor digitorum communis (EDC) and biceps brachii (BB) muscles of the side contralateral to rTMS site. TMS “motor hotspot” for EDC is identified as the location at which the lowest TMS intensity generates motor evoked potentials (MEPs) ≥100μ*V* above slight baseline contraction (20–30% of maximum voluntary contraction) in 6 of 10 trials—also termed as active motor threshold (AMT). AMT is expressed as %maximum stimulator output (%MSO). rTMS is subsequently delivered at a sub-threshold intensity of 90%AMT. If ipsilesional AMT cannot be defined due to the absence of MEPs, rTMS is applied at 72% MSO, a common and safe practice in the study of stroke survivors with severe impairment (11).

In the iM1 group, rTMS is delivered to the ipsilesional motor hotspot, unless that hotspot cannot be identified, in which case mirror location of the contralesional motor hotspot is targeted. In the cHMC group, rTMS is targeted to a region 2 cm anterior and 1 cm medial to the contralesional motor hotspot, corresponding to the location of premotor cortex (PMC) and adjoining supplementary motor area (SMA) complex (16). In the sham group, rTMS is targeted to the iM1 site or the cHMC site (randomized assignment).

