## 2. Methods

### 2.1. Participants

This study is a randomized, sham-controlled, and double-blinded clinical trial of up to 72 participants who had suffered a stroke at least 6 months previously and who continue to experience severe chronic upper limb motor impairment. Clinical assessment of the motor impairment is performed by an occupational therapist. “Severe” motor deficit is being defined as the inability to extend wrist ≥10-degrees, extend/abduct thumb ≥10-degrees, or extend two other digits ≥10-degrees (exclusion criteria in CIMT studies). This clinical motor criterion was chosen because it has a better prospect of being generalizable and was also used to define “severe” motor impairment in the previous CCFES clinical trial (2). Participants are required to have functional paretic hand opening in response to neuromuscular electrical stimulation of finger or thumb extensors to ensure it is feasible for them to undergo CCFES-mediated rehabilitation (See Inclusion Criteria, Table 1). Participants are excluded for contraindications to TMS and magnetic resonance imaging (MRI), including cardiac pacemaker, history of seizures, substance abuse, metallic implant in the head etc. determined by a stroke neurologist (See Exclusion Criteria, Table 2). Participants are being recruited from the Cleveland Clinic, Cleveland, OH. The trial is governed by human research protection policies of the Cleveland Clinic Institutional Review Board. All participants provide written informed consent before participating.

**Table 1 T1:** Inclusion criteria.

• Age 18–90 years old at the time of randomization
• >6 months since a first clinical cortical or subcortical, ischemic or hemorrhagic stroke
• Severe upper limb hemiparesis defined as lacking ≥10-degrees active wrist extension or ≥10-degrees active thumb abduction/extension or ≥10-degrees active extension in at least two additional digits (i.e., will not meet minimum constraint induced movement therapy criteria)
• Memory of at least 2 out of 3 items after 30 min
• Able to perform 3-stage command
• Full volitional hand opening/closing of the non-paretic hand
• Ability to follow instructions for putting on and operating the contralaterally controlled functional electrical stimulation (CCFES) device or have a caregiver available to provide assistance

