### 4.3. Neurophysiological Assessments

Neurophysiologic assessments are performed using TMS (Magstim 200^2^, The Magstim Company, U.K.). A 70 mm figure-of-eight TMS coil capable of delivering 100μs monophasic pulses is positioned tangentially over the scalp at locations corresponding to motor hotspots while participants are seated with their forearms supported on a flat surface. Coil placement and targeting are guided using MRI-stereotaxy. Surface 1.8 inch diameter EMG electrodes (Adult Tape ECG Ultratrace^®^ Wet Gel, Conmed Corporation, USA) are applied over the paretic and non-paretic EDCs to record MEPs and changes in ongoing muscle activity. EDC is the muscle of choice because it is the primary target muscle for CCFES, and return of MEPs in EDC will signify restoration of substrates mediating finger extension, a movement generally impaired after stroke and one that carries high clinical value (24). TMS is used to assess inter-hemispheric inhibition (IHI) and excitability of ipsilateral (uncrossed) pathways to the paretic hand. IHI is measured using the ipsilateral silent period (iSP) method (25). iSP is believed to reflect IHI imposed from the targeted motor cortex upon activity of the active ipsilateral limb (25). Excitability of ipsilateral (uncrossed) pathways to paretic muscles are measured using ipsilateral MEPs (iMEPs) evoked with TMS pulses delivered to contralesional motor regions. iMEPs are collected from the paretic biceps brachii (BB) muscle (in addition to the paretic EDC muscle) because uncrossed pathways preferentially innervate motoneurons devoted to proximal flexor muscle groups (26). Additional secondary assessments include metrics of excitability of ipsilesional and contralesional pathways to paretic and non-paretic EDC muscles, respectively (See Schedule of Assessments, Table 3).

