## 9. Summary and Conclusions

We hypothesize that the combination of CCFES with rTMS facilitation of cHMC will produce greater reduction in motor impairment and perceived disability, and larger gains in functional ability compared to CCFES with rTMS facilitation of iM1 and CCFES with sham rTMS. Findings in line with our hypothesis would reveal that intact contralesional regions make more significant contributions to movement recovery than damaged ipsilesional regions in chronic stroke survivors with severe damage and impairment.

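### The pooled cHMC versus iM1 contrast compares two stimulation strategies as delivered; alone it does not support the Section 9 statement about which brain regions contribute more to recovery

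*Protocol article*

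**What the plan says.** All references are to the protocol article.

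- **Default intensity (Section 3.1).** After the active motor threshold (AMT) is found, "rTMS is subsequently delivered at a sub-threshold intensity of 90%AMT". EMG is recorded from the "muscles of the side contralateral to rTMS site", so the threshold comes from the paretic arm for iM1 and the non-paretic arm for cHMC.
- **iM1 site (Section 3.1).** The ipsilesional hotspot is used, "unless that hotspot cannot be identified, in which case mirror location of the contralesional motor hotspot is targeted".
- **iM1 intensity without MEPs (Section 3.1).** "If ipsilesional AMT cannot be defined due to the absence of MEPs, rTMS is applied at 72% MSO". The text describes this as usual in survivors with severe impairment.
- **cHMC site (Section 3.1).** "rTMS is targeted to a region 2 cm anterior and 1 cm medial to the contralesional motor hotspot". No fallback is stated for site or intensity.
- **Population (Section 2.1, Table 1).** "Severe upper limb hemiparesis defined as lacking ≥10-degrees active wrist extension", or similar deficits of thumb or fingers. An ipsilesional MEP is not required.
- **Balancing (Section 2.2).** The four factors are time since stroke, lesion type, active wrist extension and dominance of the paretic side. MEP status is not one of them.
- **Analysis (Section 7).** Adjusted least squares means compare cHMC with iM1 and with sham across all participants. No comparison by MEP status or delivery mode is stated.
- **Conclusion (Section 9).** Findings in line with the hypothesis are to be read as showing that "intact contralesional regions make more significant contributions to movement recovery than damaged ipsilesional regions".

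**The concern.** The two active arms are meant to differ in the region stimulated. In iM1 participants without ipsilesional MEPs they also differ in how site and intensity are set: a mirrored location and a fixed output, against a location and threshold from a hotspot found in that hemisphere. This second difference can arise in only one of the two arms, and the eligibility criteria select the people in whom the protocol itself foresees it.

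If cHMC does better than iM1 overall, two explanations remain. Contralesional regions may contribute more to recovery, or iM1 stimulation may have been less effective in the fallback participants because of how it was delivered. The pooled contrast returns one number and cannot divide it between them. What is at stake is the mechanistic sentence in Section 9, not the randomised comparison itself.

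**Working it through.** **1. Delivery in the two active arms (Section 3.1)**

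| | iM1, MEP present | iM1, MEP absent | cHMC |
|---|---|---|---|
| Site | own ipsilesional hotspot | mirror of own contralesional hotspot | fixed offset from own contralesional hotspot |
| Intensity | 90% of ipsilesional AMT | fixed 72% of maximum output | 90% of contralesional AMT |

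The cHMC intensity is inferred: EMG is contralateral to the rTMS site, and the 72% rule is tied to the ipsilesional AMT only. The pooled contrast averages the first two columns and compares them with the third.

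**2. The plan's own figure**

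Section 6 plans a 5.2-point difference with SD 6 for cHMC versus sham: 5.2 / 6 = 0.87. A two-sided two-sample t-test at 0.05 with 80% power needs 21.9, so 22 per group, as stated (power at 22 is 80.2%). No figure is given for cHMC versus iM1.

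**3. How large the mixing could be**

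This is an illustration, not an estimate. Assume that cHMC and hotspot-based iM1 stimulation each have a true effect of 5.2 points, that a share p of the iM1 arm is on the fallback, and that the fallback retains a fraction r of the effect (0 to 1). The document gives neither p nor r.

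Apparent cHMC minus iM1 difference = p × (1 − r) × 5.2.

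The chance of a significant result uses SD 6, 22 per arm and two-sided 0.05.

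| p | r = 0: points (chance) | r = 0.5: points (chance) |
|---|---|---|
| 0 | 0 (5%) | 0 (5%) |
| 25% | 1.3 (11%) | 0.65 (6%) |
| 50% | 2.6 (29%) | 1.3 (11%) |
| 75% | 3.9 (56%) | 1.95 (18%) |
| 100% | 5.2 (80%) | 2.6 (29%) |

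**4. What a comparison in MEP-present participants could show**

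There both active arms are set from a measured hotspot and threshold. With 72 / 3 = 24 per arm and an assumed MEP-absent share of 30% to 70%, about 24 × 0.3 = 7 to 24 × 0.7 = 17 per arm would have MEPs. The 95% half-width is t × 6 × √(2/n):

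- n = 7: 2.179 × 3.207 = 7.0 points; power for 5.2 points about 32%.
- n = 17: 2.037 × 2.058 = 4.2 points; power about 69%.

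Such an estimate is informative if positive, but too imprecise to settle the question if it is not.

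**The case against.** **Absent MEPs are part of the hypothesis.** Sections 1 and 8 argue that iM1 stimulation fails where ipsilesional pathways are badly damaged. A poor iM1 result in MEP-absent participants is then the predicted result, and hotspot-based delivery is not possible there. This stands. It keeps the contrast valid as a comparison of strategies and makes delivery mode partly inseparable from the condition studied. It does not turn that contrast into evidence about regions.

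**The asymmetry is easily overstated.** One might infer that iM1 fallback stimulation is untargeted while cHMC stimulation is fully calibrated. The text supports neither. The mirror site comes from the participant's own contralesional hotspot, under MRI-guided stereotaxy. The cHMC site is a fixed offset from the primary motor hotspot, dosed from that hotspot's threshold, with no physiological confirmation at cHMC. Nor does the document show whether the fixed output is more or less than a threshold-based dose would have been.

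**A subgroup test does not cleanly separate the explanations.** The protocol's reasoning predicts the smallest cHMC advantage in MEP-present participants, and MEP status also tracks severity. This stands too: no difference in that stratum would fit both explanations.

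**Subgroup estimates and fallback counts often sit in an analysis plan, which is not shown.** True, and their absence is not the fault raised here. The fault is the inference written in Section 9. Section 7 does plan regressions of response on baseline impairment, lesion and corticospinal damage, but as described they do not give cHMC minus iM1 by MEP status.

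**Conclusion.** The concern holds for one sentence. The pooled cHMC minus iM1 contrast is a valid comparison of two stimulation strategies as delivered, but alone it does not support the regional conclusion in Section 9.

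Three stronger readings are tempting and not supported:

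- **That the contrast is invalid, or a cHMC win an artefact.** Under equal 5.2-point effects the distortion runs from 0 to 5.2 points. Assumed shares of 30% to 70% give 1.6 to 3.6 points (0.3 × 5.2 and 0.7 × 5.2), but only if the fallback has no effect at all. Both inputs are assumptions, as is carrying the cHMC versus sham difference over to iM1. The range also assumes that the fallback does no better than hotspot-based delivery.
- **That the Section 8 claim of cHMC being an appropriate target falls too.** That is a statement about strategy, which the contrast as delivered can support.
- **That cHMC versus sham is compromised.** The iM1 fallback does not affect it in this way.

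The actual size cannot be determined from the document.

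**What to change.** Leave delivery unchanged; nothing here says which site or intensity rule is right.

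1. **Section 9:** restate the conclusion as a comparison of two stimulation strategies in survivors with severe impairment.
2. **Reporting:** state how many iM1 participants received the mirror site, the fixed output or both. Take this from the rTMS session records, not from the week-0 TMS session: Section 4.3 uses a different stimulator with monophasic pulses, whereas Section 3.1 delivers biphasic pulses, so the two need not agree on who lacked MEPs.
3. **Section 7:** add a supportive cHMC minus iM1 estimate with confidence interval by baseline ipsilesional MEP status. No new data are needed: Table 3 schedules TMS at week 0, and Section 4.3 states that "Additional secondary assessments include metrics of excitability of ipsilesional and contralesional pathways to paretic and non-paretic EDC muscles", respectively.
4. **Interpretation, stated in advance:** a difference in MEP-present participants would support the regional reading. Its absence there would be inconclusive, because the stratum is small and the hypothesis itself predicts a smaller advantage.

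The cost is one imprecise extra estimate and a more modest conclusion. Rewording Section 9 alone already removes the error.

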### 3.2. CCFES Therapy

Immediately after completing rTMS, participants engage in 1 h of therapist-guided, CCFES-mediated functional task practice in the laboratory. The CCFES stimulator delivers biphasic rectangular current pulses at a pulse frequency of 35 Hz and pulse amplitude of 40 or 60 mA (2). A pulse frequency of 35 Hz was chosen because it creates fused muscle contractions without inducing muscle fatigue as rapidly as higher frequencies (17). Up to 3 channels of stimulation are programmed to produce hand opening. Surface electrodes are positioned to activate the EDC and extensor pollicis longus (EPL). Abductor pollicis brevis (AbPB), dorsal interossei (DI), or extensor indicis proprius (EIP) may also be targeted if they are necessary to achieve functional hand opening. This process of determining electrode locations and stimulus parameters is done only once, and in a separate session prior to the first rTMS and CCFES therapy session. The CCFES stimulator is programmed to increase pulse duration for each stimulating electrode in proportion to the amount of opening of an instrumented glove worn on the contralateral non-paretic hand.

Early sessions of CCFES therapy focus on simpler tasks, such as practicing opening the hand adequately to acquire an object. Task difficulty progresses from easy-to-acquire-and-manipulate to tasks requiring wider hand opening, greater complexity, skill, and coordination of hand function with proximal upper limb movement. Hands-on assistance and strengthening are provided as necessary to reinforce correct movement patterns. Weight bearing and stretching are used to overcome spasticity and allow movements that are more effective.

### 3.3. Self-Administered Home Therapy

An instruction manual is provided to every participant, and they are trained to perform CCFES hand opening exercises at home. Each home session consists of three 15-min periods separated by 3 min of rest (45 min of work per session). During each 15-min period, the stimulator issues audio and visual cues prompting the participant to attempt to fully open both hands for several seconds, then relax both hands for several seconds, and repeat the cycle. Adherence to the home stimulation regimen is monitored with participant diaries and electronic data logging by the stimulator at every visit during the treatment period. The therapist checks patient diaries and logs stimulator usage data before beginning each therapy visit in the laboratory. In addition, the therapist monitors how patient engages in CCFES-based exercises at home by observing them in the laboratory while performing CCFES ( 10 min). The mean (SD) percentage of compliance of CCFES device use was recorded to be 96% (8.7%) (2) in our previous study and we expect similar results in our ongoing study.

## 4. Outcome Measures

Upper limb impairment, activity limitation, and patient-reported disability are assessed at 0 (baseline), 6 (mid-treatment), 12 (end-of-treatment), 24 (3-month follow-up), and 36 weeks (6-month follow-up) (Figure 1). Neurophysiological assessments are performed at 0, 12, and 36 weeks, on a separate day from the motor assessments. Imaging assessments are performed at 0 and 12 weeks (See Schedule of Assessments, Table 3). Subjects refrain from using their CCFES stimulators for 24 h prior to their 6-week and 12-week assessments in order to avoid any transient carry over effects or muscle fatigue.

**Figure 1 F1:**
[figure not shown]
Overview of study design showing the timeline, intervention, and outcome measures. UE, upper extremity; TMS, transcranial magnetic stimulation; CCFES, contralaterally controlled functional electric stimulation.

**Table 3 T3:** Schedule of assessments.

**Outcome measures**	**Week**				
	**0**	**6**	**12**	**24**	**36**
**Motor Impairment and Function Assessments**					
Upper Extremity Fugl Meyer (UEFM)	X	X	X	X	X
Wolf Motor Functional Test (WMFT)	X	X	X	X	X
Stroke Upper Limb Capacity Scale (SULCS)	X	X	X	X	X
Stroke Impact Scale (SIS-16)	X	X	X	X	X
Range of Motion (ROM)	X	X	X	X	X
Modified Ashworth Scale (MAS)	X	X	X	X	X
Patient Health Questionnaire (PHQ-9)	X	X	X	X	X
Leisure-Time Exercise Questionnaire (LTEQ)	X	X	X	X	X
**Neurophysiological and Motor Control Assessments**					
Transcranial Magnetic Stimulation (TMS)	X		X		X
Hoffman-Reflex (H-Reflex)	X		X		
Grip Force	X		X		X
Maximum Voluntary Contraction (MVC)	X		X		X
Bilateral Task	X		X		
**Neuroimaging Assessments**					
Magnetic Resonance Imaging (MRI)	X		X		
Diffusion Tensor Imaging (DTI)	X		X		
Functional MRI (fMRI)	X		X		
Resting state fMRI (rs-fMRI)	X		X		
**Self-Assessment of Treatment**					
Blinding Integrity			X		
End of Treatment Questionnaire			X		

*X indicates that the outcome measure will be assessed at that time point*.

### 4.1. Primary Outcomes

The primary endpoint is the change in upper-limb motor impairment at the end-of-treatment, as assessed by the Upper Extremity Fugl Meyer (UEFM) score. The UEFM is a reliable and valid measure of post-stroke upper limb motor impairment (18) that evaluates a participant's ability to perform upper extremity motions both in and out of synergy and with respect to both proximal and distal joints. The minimal clinically important difference (MCID) for UEFM in chronic stroke survivors with minimal to moderate impairment is a 4.25-point gain (3) and achievement of this at end-of-treatment will qualify as a clinically significant improvement/response. Other definitions of therapeutic response will also be compared to find convergence, including attaining response at secondary endpoints (12-wk, 24-wk follow-up) or a composite score based on impairment and functional ability measures or treatment induced gain.

### 4.2. Secondary Outcomes

#### 4.2.1. Behavioral Outcome Measures

Secondary measures listed in priority order include Wolf Motor Function Test (WMFT) rate for measuring motor function (19), Stroke Upper Limb Capacity Scale (SULCS) for measurement of upper-limb capacity (20), Modified Ashworth Scale (MAS) for evaluation of spasticity (21), grip strength (dynamometry), range of wrist extension, Stroke Impact Scale (SIS-16) for measuring patient-reported disability (22), and Leisure-time Exercise Questionnaire for measuring physical activity (23).

### 4.3. Neurophysiological Assessments

Neurophysiologic assessments are performed using TMS (Magstim 200^2^, The Magstim Company, U.K.). A 70 mm figure-of-eight TMS coil capable of delivering 100μs monophasic pulses is positioned tangentially over the scalp at locations corresponding to motor hotspots while participants are seated with their forearms supported on a flat surface. Coil placement and targeting are guided using MRI-stereotaxy. Surface 1.8 inch diameter EMG electrodes (Adult Tape ECG Ultratrace^®^ Wet Gel, Conmed Corporation, USA) are applied over the paretic and non-paretic EDCs to record MEPs and changes in ongoing muscle activity. EDC is the muscle of choice because it is the primary target muscle for CCFES, and return of MEPs in EDC will signify restoration of substrates mediating finger extension, a movement generally impaired after stroke and one that carries high clinical value (24). TMS is used to assess inter-hemispheric inhibition (IHI) and excitability of ipsilateral (uncrossed) pathways to the paretic hand. IHI is measured using the ipsilateral silent period (iSP) method (25). iSP is believed to reflect IHI imposed from the targeted motor cortex upon activity of the active ipsilateral limb (25). Excitability of ipsilateral (uncrossed) pathways to paretic muscles are measured using ipsilateral MEPs (iMEPs) evoked with TMS pulses delivered to contralesional motor regions. iMEPs are collected from the paretic biceps brachii (BB) muscle (in addition to the paretic EDC muscle) because uncrossed pathways preferentially innervate motoneurons devoted to proximal flexor muscle groups (26). Additional secondary assessments include metrics of excitability of ipsilesional and contralesional pathways to paretic and non-paretic EDC muscles, respectively (See Schedule of Assessments, Table 3).

